#### Parents

The target population for the intervention are parents of preschool children: mothers, fathers and carers (e.g. with children living in stable/long-term foster care).Parents must have at least one child aged between 6 months and 5 years. If more than one child in the family fulfils eligibility criteria, the youngest child (by birth timing if twins) will be considered as the reference child (about whom data will be collected).Parents must be willing to attend the programme sessions (intervention centres) and willing to provide data in accordance with the data collection protocol. Parents will be provided with full details of the data collection requirements in advance so that they can make informed decisions as to whether to participate.Parents must speak English (the intervention and data collection forms are currently only available in English), unless they wish to bring their own interpreter with them (e.g. family member).

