### Feasibility outcomes

The feasibility outcomes were as follows:Recruitment rate, including number of local authorities screened for eligibility, reason for ineligibility and number (and reason) for declining; number agreeing to take part (including number of nominated centres); number of centres agreeing to take part (and reason for those declining); number of parents approached; number (and proportion) agreeing to researcher contact; number (and proportion) of eligible parents consenting; number of parents self-referring; and reasons for parent ineligibility and non-consent.Training and quality assurance, including length of time taken to train and certify staff to deliver HENRY programme; number of staff attending training; number of staff certified to delivery HENRY; changes in knowledge and practice before and after training (from pre and post training facilitator questionnaire); and programme delivery quality assurance (collected routinely by HENRY).Contamination identification and risk, ascertained through determining the number of parents registered to control centres attending centres running HENRY; HENRY-trained facilitators working in or visiting control centres and proportion of their time spent working in other centres; control and intervention centres merging with other centres; other schemes addressing lifestyle change attended by parents during the study; parents registered to control centres who have had contact with parents attending centres running HENRY. We will also assess the frequency of contact between parents in HENRY and control centres. Risk will be estimated by triangulating identified sources of contamination with outcome data and qualitative assessment of perceived contamination.Acceptability of data collection protocol, assessed from the number, proportion and timing of parent withdrawals from HENRY programme (intervention centres only) and follow-up data collection (both parents registered to HENRY and control centres) out of those registered and reasons for withdrawal; number (and proportion) of registered parents lost to follow-up; number (and proportion) of parents with self-reported questionnaire and height/weight data; and missing item level data on questionnaires. Feedback will be gathered from parents, centre staff and commissioning leads via interviews and focus groups.Determination of sample size for definitive trial estimated using feasibility data: variability of gender-adjusted body mass index (BMI) in both arms; difference between arms and 95% confidence intervals; and estimation of clustering effect (ICC) and cluster size.Intervention compliance and implementation, estimated from routinely gathered data on timing of delivery of first HENRY programme (plus reasons if delivery occurs later than 4 weeks after training); number of HENRY courses delivered per centre; and attendance rates at HENRY programmes and reasons for absence.

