#### Primary outcome

The primary outcome was reference child BMI z-score (age- and gender-adjusted height(m)/weight(kg)^2^) measured by NatCen interviewers.

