Participant retention during follow-up, including the number of centres/parents withdrawing from the study and the timing of and reasons for the withdrawal will be presented overall, by arm and time-point. We will also report losses to follow-up over time. We will also report the difference and its confidence intervals (CI) for follow-up rates between the intervention and control groups (to identify large differences between the arms). Levels of missing self-reported outcome data, both at the individual item level and for entire outcome measures will be reported overall, by time-point and by treatment arm.

Centre environment, family eating/activities, parenting self-agency, pre-schooler feeding and dental health at baseline and at 12 months post registration will be summarised overall, by arm and by time-point and where appropriate by centre (centre environment). 95% CI will be constructed for the differences in these outcomes between control and intervention groups. Mean activity per day will be summarised overall, by arm and by time-point.

In order to inform the sample size calculation for the definitive trial, we will calculate the gender-adjusted BMI, overall and per arm together with corresponding 95% CI. We will also compare the variability of gender-adjusted BMI between arms. As variation surrounding the intra-class correlation coefficient (ICC) estimate is likely to be large, we will estimate the ICC after controlling for covariates and constructing a CI [34, 36] to obtain a range of plausible estimates from which a variety of sample sizes can be calculated. A conservative approach would be to use the 80% upper one-sided confidence limit of the ICC estimate [34] in the sample size calculations.

To assess compliance with and fidelity of delivery of HENRY, the timing of delivery of the first HENRY programme will be summarised overall and by centre. Reasons for delivery post 4 weeks after receiving training will be presented by centre. In addition, the number of HENRY programmes delivered per centre, attendance rates and reasons for absence will be presented.

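### The BMI summaries meant to inform the definitive trial's sample size are specified on gender-adjusted BMI, while the primary outcome is the age- and gender-adjusted BMI z-score

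*Protocol article*

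**What the plan says.** The Primary outcome section of the protocol article reads: "The primary outcome was reference child BMI z-score (age- and gender-adjusted height(m)/weight(kg)^2^) measured by NatCen interviewers". It is the only child BMI measure that the article defines.

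Two other sections set out what will feed the definitive trial's sample size:

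- Feasibility outcomes, item on sample size: "variability of gender-adjusted body mass index (BMI) in both arms; difference between arms and 95% confidence intervals; and estimation of clustering effect (ICC) and cluster" size.
- Statistical analysis, paragraph on the definitive sample size: "we will calculate the gender-adjusted BMI, overall and per arm together with corresponding 95% CI", then "We will also compare the variability of gender-adjusted BMI between arms".

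On clustering, the same paragraph continues: "we will estimate the ICC after controlling for covariates and constructing a CI". That sentence names neither the outcome nor the covariates.

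The age range comes from the parent inclusion criteria: "Parents must have at least one child aged between 6 months and 5 years". The second measurement is 12 months after registration (Blinding section).

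**The concern.** Wherever the article names the variable behind the sample-size inputs, it names BMI adjusted for gender only. Age is absent all three times, and the Statistical analysis section does not mention the z-score. An analyst who followed that section literally would summarise a quantity that is not the primary outcome.

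Two things then go wrong. First, the SD would be in kg/m² and could not be set against a target difference in z-score units. Second, it would contain whatever variance comes from mean BMI changing with age over a span of several years. The article's own choice of an age-adjusted primary outcome accepts that BMI depends on age.

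Age mix could also differ between centres and arms. Intervention parents are recruited when they enrol on HENRY, and control parents from other activities in the centre (Recruitment and consent, Parents). If the ICC and arm difference are also computed without age adjustment, such differences would carry into them.

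**Working it through.** **1. No stated figure to reproduce.** The article gives no SD, ICC, target difference or power for the definitive trial. Its own size is a rule of thumb of at least 30 per group. The counts agree with each other: 120/12 = 10 parents per centre, and 120/2 = 60 per arm.

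**2. Which parameter is tied to which variable.**

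| Quantity | Feasibility outcomes | Statistical analysis |
|---|---|---|
| Level of BMI | not listed | gender-adjusted BMI, overall and per arm |
| Variability | gender-adjusted BMI, both arms | gender-adjusted BMI, compared between arms |
| Arm difference | listed, no variable named | none stated for child BMI |
| ICC | listed, no variable named | no outcome named; unnamed covariates |

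The mismatch with the primary outcome is explicit for level and variability. For the ICC and the arm difference it is inferred from their position beside gender-adjusted BMI.

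**3. Age span.** Entry is at 6 months to 5 years and follow-up is at 12 months, so ages reach about 5 + 1 = 6 years.

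**4. Illustration of size. Every input here is assumed; none comes from the document.** Let s be the within-age SD of BMI (1.2 or 1.5 kg/m², taken as one z unit), and a the SD of the age-specific mean BMI (0 to 0.9 kg/m²). Let f be the share of age variance lying between centres (0 to 0.20). The z-score ICC is 0.02, the cluster size m is 10, the true difference is 0.25 z (0.25s in kg/m²), two-sided alpha is 0.05 and power is 0.80.

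- Variance ratio = 1 + (a/s)²
- ICC without age adjustment = (0.02s² + f·a²)/(s² + a²)
- Design effect = 1 + (m − 1)·ICC

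On the z-score itself: 252 per arm unclustered; 252 × (1 + 9 × 0.02) = 297.4, so 298 with clustering.

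| s | a | Variance ratio | n/arm, unclustered | ICC at f = 0 → 0.20 | n/arm, clustered, at f = 0 → 0.20 |
|---|---|---|---|---|---|
| 1.2 | 0 | 1.00 | 252 | 0.020 → 0.020 | 298 → 298 |
| 1.2 | 0.3 | 1.06 | 267 | 0.019 → 0.031 | 313 → 341 |
| 1.2 | 0.6 | 1.25 | 314 | 0.016 → 0.056 | 360 → 473 |
| 1.2 | 0.9 | 1.56 | 393 | 0.013 → 0.085 | 439 → 693 |
| 1.5 | 0.3 | 1.04 | 262 | 0.019 → 0.027 | 308 → 326 |
| 1.5 | 0.6 | 1.16 | 292 | 0.017 → 0.045 | 338 → 410 |
| 1.5 | 0.9 | 1.36 | 342 | 0.015 → 0.068 | 388 → 551 |

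Worked cell, s = 1.2, a = 0.9, f = 0.20: variance ratio 1 + 0.81/1.44 = 1.5625; ICC (0.0288 + 0.162)/2.25 = 0.0848; n = 393 × (1 + 9 × 0.0848) = 692.9, so 693.

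**5. Direction for the ICC.** From the formula, the unadjusted ICC exceeds the z-score ICC only when f is greater than that ICC (here 0.02). If ages are well balanced across centres, the extra age variance sits within centres and dilutes the ICC. The bias can therefore go either way.

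**The case against.** The strongest reply is that gender-adjusted BMI is loose shorthand for the z-score. The article defines no other child BMI outcome, and its BMI wording is imprecise elsewhere: the formula is printed as height over weight squared. That reading is plausible, but it does not dispose of the point. The article names a variable three times, and each time it differs from the primary outcome, so this is a conflict and not detail left to an analysis plan. If it is shorthand, the same rewording settles it.

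A second reply concerns reach, and it stands. A reader might infer that the plan puts the ICC and arm difference on the wrong variable as firmly as the SD. The text does not support that. The ICC sentence names no outcome, its covariates could include age, and the Statistical analysis section states no arm difference for child BMI.

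A third reply concerns consequence, and it also largely stands. Estimating the sample size is a secondary objective (Objectives) with no progression cutoff (Progression rules for definitive trial). The z-score is only a candidate outcome for the later trial (Intervention impact measures), and no hypothesis test is planned. Nothing in recruitment, randomisation or data collection depends on the wording.

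**Conclusion.** The inconsistency is real. The level and variability of BMI that are to inform the definitive sample size are specified on a variable not adjusted for age, and the primary outcome is adjusted for age. Taken as written, the resulting SD cannot size a trial on the z-score. The ICC and arm difference are affected only if, as the context suggests, they use the same variable.

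The size cannot be derived from the document. The variance ratio of 1.00 to 1.56 and the ICC range of 0.013 to 0.085 rest wholly on the assumed spread of mean BMI with age, the within-age SD, the z-score ICC and the between-centre share of age variance. If mean BMI did not vary with age (a = 0), the variance ratio and ICC would be unchanged and only the units would differ. A reader might infer that the definitive trial would necessarily be oversized, or that the sample-size objective is lost. Neither follows: the ICC can move in either direction, and the correct quantities can be recomputed from data that the primary outcome already requires. Severity is moderate.

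**What to change.** In the sample-size item of Feasibility outcomes and in the corresponding paragraph of Statistical analysis, replace gender-adjusted BMI with BMI z-score (age- and gender-adjusted). In both places, name the z-score as the outcome for the SD, the arm difference and the ICC.

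The cost is a wording change. No data are needed beyond those that the primary outcome already requires.

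Reporting the baseline to 12-month correlation of the z-score would also help whoever sizes the definitive trial, but it is optional and does not follow from the mismatch.

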### Data monitoring and confidentiality

Missing local authority and children’s centre demographic and screening data will be chased until it is received, confirmed as not available or if the analysis by CTRU has started. Parent data will be monitored for quality and completeness by the NatCen research team prior to its transfer to the CTRU. Data provided to the CTRU will be monitored for quality and completeness by the CTRU. Monthly data query reports will be generated by CTRU and forwarded to the NatCen research team.

All data provided will be stored, handled and processed in accordance with the principles of the 1998 Data Protection Act and ISO 27001, and specific strategies will be used to maintain anonymity and confidentiality. Operationally, this will include the following:Local authority and parent level screening data (containing data on local authorities/centres/individuals that decline).Where documentation is required that includes identifiable information from sites, e.g. postcode, data will be posted to the CTRU and stored securely in a separate location to study data.Participant contact details will be collected by children’s centres during screening and posted to NatCen to facilitate study registration. These data will be posted to NatCen in batches via secure tracked mail.Participant contact details will be transferred to CTRU so trial reminders can be sent and a selection of participants can be invited to take part in the focus group. This data will be transferred to CTRU via the secure data transfer system and stored securely at CTRU in a separate location to study data.All study data collected from participants will be transferred from NatCen to CTRU via post and will be coded with a unique study ID and two identifiers (the participant’s initials and date of birth).If a local authorities/centres or parents withdraw consent from further collection of data, the existing data that they have provided up to the date of withdrawal will remain on file and will be included in the final study analysis.

### Trial oversight

The Trial Steering Committee will provide oversight for the study. In particular, they are responsible for monitoring the study progress, adherence to protocol, participant safety and consideration of new information. It includes an independent chair and three other independent members, including an experienced trial statistician. The chief investigator and other members of the internal project team attend all FSC meetings and present and report progress. The FSC operates in line with the CTRU’s Committee terms of reference (ToR) as amended and agreed by FSC members at their first meeting.

A Study Management Group (chaired by [name]), comprising the chief investigator, CTRU team ([name], [name], [name]) and health economist ([name]) will be assigned responsibility for the set-up, ongoing management and promotion of the trial. This includes (i) protocol completion, (ii) data collection requirements, (iii) obtaining ethical approval, (iv) completing cost estimates and project initiation, (vi) facilitating the FSC, (vii) monitoring of site conduct and (vii) interpretation of results and contribution to publications. The SMG will operate in line with the agreed ToR.

For a trial of this nature and duration, a separate Data Monitoring and Ethics Committee is not required. Rather, the Steering Committee will adopt a safety monitoring role, with the constitution of a subcommittee to review safety issues where this becomes necessary.

The sponsor (University of Leeds) has the right to conduct source verification although this is not anticipated given safety and efficacy are not endpoints of this study. The rights for the data belong to the Study Sponsor, and no processing, including further data transfer in whole or in part to a 3rd party, is permitted other than as stated in the data transfer agreements.

To ensure responsibility and accountability for the overall quality of care received by participants during the study period, clinical governance issues pertaining to all aspects of routine management will be brought to the attention of the Trial Steering Committee and, where applicable, to individual local authorities and/or children’s centres. NatCen interviewers will follow standard NatCen safeguarding procedures. If a disclosure issue is raised by an interviewer during a home visit, details will be sent via email to the Director of Field to review, and, if necessary, the issue will be referred to the NatCen disclosure board.

### Trial organisation and administration

The trial is sponsored by the University of Leeds and co-ordinated by the CTRU (Clinical Trials Unit, University of Leeds, [name]). The management group consists of the chief investigator and the study management group. Protocol amendments will be handled in accordance with relevant Health Research Authority (HRA) guidance and CTRU standard operating procedures. Amendments required to the protocol and ethically approved documents will be identified by the trial researcher and the chief investigator and submitted to the School of Medicine Research Committee for ethical opinion prior to implementation. A list of amendments will be included in the final report.

A parent advisory group (consisting seven parents of preschool children) has been convened to support all aspects of the trial. The parent advisory group meet locally twice a year to provide feedback on aspects such as study design (e.g. consideration of control group), parent recruitment (e.g. strategies to recruit and recommendations for incentives) and data collection (highlighting sensitive items requiring more consideration). Moving forward, they will also help interpret the data and with engagement and dissemination activities. Feedback from the parent advisory group meetings is reported back to the steering committee via the research team and via a member of the parent advisory group who also sits on the Trial Steering Committee.

### Publication policy

The success of the research depends upon the collaboration of all partners. For this reason, credit for the main results will be given to all those who have collaborated in the research, through authorship and by contribution. Uniform requirements for authorship for manuscripts submitted to journals will guide authorship decisions (www.icmje.org). These state that authorship credit should be based only on substantial contribution to the following:Conception and design, or acquisition of data, or analysis and interpretation of dataDrafting the article or revising it critically for important intellectual contentFinal approval of the version to be publishedAnd that all these conditions must be met.

Other acknowledgements to the steering committee, the parent advisory group, members of the HENRY team, NatCen, participants and others will be agreed and included as appropriate.

The first author is responsible for the submission of the publication and must keep the HENRY central office team and all authors informed of the abstract’s or manuscript’s status. The steering committee will be kept informed of rejections and publications as these occur. On publication, the first author should send copies of the abstract and manuscript to the steering committee, the SMG, the Sponsor and to all other co-authors and ensure communication with the funder as per the contractual agreement.

## Discussion

Childhood obesity impacts physiological and psychological health that tracks into adulthood, increasing risk of morbidity and mortality [37, 38]. It incurs significant costs on the UK economy, with an expected sevenfold increase in related NHS costs by 2020, and forecasted £2 billion annual spend by 2030 [39]. Tackling obesity is a key NHS public health priority, and programmes to treat and prevent it are commonly commissioned in local authorities. Evidence of such programmes from randomised controlled trials is lacking. It is acknowledged that many local authorities commission a range of programmes, despite their lack evidence base. The urge to favour action over evidence is understandable given current rates of childhood obesity. However, we argue that demonstration of effectiveness and cost-effectiveness is fundamental to support the prioritisation of tax payer’s spending. The HENRY programme is an intervention with preliminary evidence suggesting high levels of parent acceptability and trends in increasing positive healthy weight behaviours in those attending [18, 22]. Over 10,000 families have already attended the HENRY programme, funded through public money; it is therefore important to establish its effectiveness.

The proposed feasibility study will support decision making in a future definitive trial. If any of the progression criteria are not met, future assessment of the effectiveness of the HENRY programme will be negotiated. Other findings such as the identified risk and impact of contamination will support a potential re-design of a trial, for example, to consider the ability to conduct individual level randomisation in existing HENRY areas to increase our recruitment pool. However, further feasibility testing may be needed prior to the conduct of a definitive trial in this eventuality. During our design phase, we undertook consultation with stakeholders, including local authorities, parents, our Trial Steering Committee, HENRY central office and methodologists within the CTRU. There was initial concern that the local authority commissioners would not agree to have centres randomised to HENRY or not, particularly as such programmes are often commissioned to support disadvantaged families. An alternative stepped wedge design was proposed so that, by the end of the trial, all centres would be randomised to HENRY. While deemed to be acceptable, issues with contamination (e.g. control parents attending the same centre as active parents), the requirement to host multiple training sessions after each randomisation and the impact of calendar time and facilitator learning curve on outcomes meant that a stepped wedge design was not pursued further. Importantly, our discussions with commissioners revealed that they were happy with both the parallel and stepped wedge designs.

The progression of this feasibility study to a definitive trial of effectiveness will provide an evidence base of an approach to prevent childhood obesity, which is attractive to all stakeholders, including parents. If deemed effective, HENRY offers extensive benefit to health, including reduced preschool obesity, improved nutrition/eating behaviours in children, healthier family lifestyles and enhanced parenting skills, reducing related morbidity and mortality. Proposed research therefore has an expressed need, not just for obesity prevention, but also to evaluate the return on investment in terms of effectiveness and cost-effectiveness of a programme that has already incurred much spending.

